## Method

### Study Design

Our study will be a parallel 12-weeks randomised control trial, involving three groups; two intervention groups (IIS and EIS) and a parallel placebo control group of participants attending the respiratory clinic at the Lagos State University Teaching Hospital, Ikeja (LASUTH).

### Participants

The participants will consist of male and female patients aged 40 years and above attending the respiratory clinic of Lagos State University Teaching Hospital, Ikeja, Lagos, Nigeria, West Africa, with spirometry confirmed obstructive, restrictive or mixed respiratory impairment for a period greater than 6 months.

The inclusion criteria are patients with COPD, IPF, ILD, cystic fibrosis, thoracic cage abnormalities (kyphosis, kyphoscoliosis, pectus carinatum or pectus excavatum) history of about or more than 6 months duration attending the respiratory clinic of LASUTH, Ikeja, Lagos. The respiratory condition of the selected participants must be spirometry confirmed to have resulted in an obstructive, restrictive or mixed respiratory airway impairment.

The exclusion criteria are patients who are on a cardiac pacemaker, supplemental oxygen therapy, those with cardiac conditions, patients with psychological impairments and patients with bronchial asthma.

### Sample size calculation

The pulmonary function test is the primary outcome of interest for our study and the expected clinically relevant difference for obstructive restrictive and mixed impairment using LLN and GLI reference equation as proposed by Quanjer et al. (1993). Therefore, the sample size (*n*) will be determined using G-Power statistics software (stats.oarc.ucla.edu). The power is selected at 95% = 0.95, confidence level at 5% = 0.05 and effect size of 0.35 (Figure 1), namely:

**F-tests – MANOVA:** Repeated measures, within-between interaction

**Options:** Pillai V, O’Brien-Shieh Algorithm

**Analysis:** A priori: Compute required sample size

**Input:** Effect size f(V) = 0.35

    α err prob = 0.05

    Power (1-β err prob) = 0.8

    Number of groups = 9

    Number of measurements = 6

**Output:** Non-centrality parameter λ = 31.2375000

     Critical F = 1.4522092

     Numerator degree of freedom (*df*) = 40.0000000

     Denominator df = 210

     Total sample size = 51

     Actual power = 0.8010637

     Pillai V = 0.5456570

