**Clinical implication:**

Our study results may indicate if inspiratory incentive spirometry or expiratory incentive spirometry is better suited for the treatment of the respiratory impairment.

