### Data analysis

The Statistical Package for Social Sciences (SPSS Inc, Chicago, Illinois, United Sates) version 26.0 for windows package programme will be used to analyse data. Descriptive statistics of mean, standard deviation, frequencies and percentages will be used to summarise the results. Bar charts, pie charts and histograms will be utilised for pictorial illustration. A multivariate analysis of variance (MANOVA) will be used to compare the outcome pulmonary function variables (FEV_1_, FVC, FEV_1_/FVC, PEFR) and QoL (6MWT, MRC dyspnoea scale score and PFSDQ-M score) among groups, while the Bonforreni’s *t*-test will be utilised for post hoc analysis to detect where significant changes occurred in the outcome variables. Dependent t-tests will be used to compare the pre- and post-test results within variables while independent t-tests will be used to compare the outcome variable among the study and control groups. The level of significance will be set at *p* ≤ 0.05.

The study does not potentially involve risk or harm, as all interventions can only be performed within the limit of the patient’s tolerance. However, participants may experience mild discomfort because of the exercise, including temporary muscle soreness, increased heart rate, blood pressure, sweating and dizziness. All necessary care will be in place to prevent the occurrence of any adverse event. However, in case of a report of serious adverse events (e.g. comorbidities, injuries, persistent excruciating pain, dizzy spells, headache, etc.) after the intervention or at any point during the trial, we would consider unblinding the participant to the intervention for their safety. Additionally, the participants will be instructed to report adverse events to the first author PI or the physiotherapist supervising their group. To ensure adequate supervision, participants per group to be attended in a day will be limited to a maximum of three. Arrangements will be made with the Accident and Emergency units of the research site to provide a standby medical team. The University of KwaZulu-Natal insurance scheme on clinical trials has fully covered participants in this type of study.

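### Four unranked spirometry variables share the primary outcome, with no deciding variable, time point or multiplicity rule across them, and unadjusted t-tests at 0.05 are planned beside the MANOVA

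*Protocol article*

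**What the plan says.** The Sample size calculation section of the protocol article defines the primary outcome: "The pulmonary function test is the primary outcome of interest for our study". No component of the test and no time point is singled out there.

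The specific objectives (Significance of our study) and the Data analysis section break the test into four variables without ranking them. Data analysis says the MANOVA "will be used to compare the outcome pulmonary function variables (FEV_1_, FVC, FEV_1_/FVC, PEFR) and QoL", where the QoL set is the 6MWT, the MRC dyspnoea score and the PFSDQ-M score.

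Three further features of Data analysis matter:

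- A Bonferroni t-test "will be utilised for post hoc analysis to detect where significant changes occurred in the outcome variables". The set of comparisons it corrects for is not given, and nothing says the MANOVA must be significant first.
- In addition, "independent t-tests will be used to compare the outcome variable among the study and control groups". No adjustment is mentioned.
- The significance level is 0.05 throughout.

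The Abstract states the intended conclusion: "Our study results may indicate if inspiratory incentive spirometry or expiratory incentive spirometry is better suited for the treatment of the respiratory impairment".

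**The concern.** The question is which therapy suits which class of impairment, and the four variables need not agree on the answer. By the article's own definitions (Background), restriction lowers FVC while the ratio stays normal, so FVC and FEV1/FVC can move differently. The expiratory arm trains by blowing maximally into a peak flow meter, so a difference seen only in PEFR is plausible.

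With no deciding variable, whichever one is significant can carry the conclusion, and that choice can be made after the data are seen. The time point is open as well: the Abstract has pulmonary function assessed before and after every procedure, and sessions run three times a week for 12 weeks (3 × 12 = 36 sessions). At stake is whether the stated 5% error rate applies to the claim the trial wants to make.

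**Working it through.** **1. The plan's own figure.** The inputs in Sample size calculation are f(V) = 0.35, α = 0.05, k = 9 groups and m = 6 measurements.

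- s = min(k−1, m−1) = 5
- df1 = (k−1)(m−1) = 8 × 5 = 40
- df2 = s(N−k−(m−1)+s) = 5 × (51−9−5+5) = 210
- λ = f²·N·s = 0.1225 × 51 × 5 = 31.2375
- Critical F = 1.4522; power from the noncentral F = 0.8011. N = 50 gives 0.789.

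The stated N of 51 is reproduced. The 40 numerator df are groups by occasions for one response, so the calculation has no term for four variables.

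**2. Independent variables, by formula.** One 5% test on each of four independent variables gives 1 − 0.95⁴ = 0.185. At 0.0125 each, it gives 1 − 0.9875⁴ = 0.049.

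**3. Correlated variables, by simulation.** The set-up was 40,000 trials per setting with no true effect, one normal value per variable, and three therapy arms of 18 (the planned 54, pooled over impairment class). Equal correlation among the four variables is an assumption. The rules compared were:

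- A: t-tests of each active arm against control, two-sided 0.05, 34 df, unadjusted
- B: three arm pairs per variable, Bonferroni within the variable only, 51 df, no gate
- C: as B, but only after a significant joint Pillai MANOVA on the four variables
- D: Bonferroni over all 3 × 4 = 12 comparisons

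Chance of at least one false positive among the four variables:

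| Correlation | A | B | C | D |
|---|---|---|---|---|
| 0.3 | 30.1% | 15.5% | 3.8% | 4.4% |
| 0.5 | 27.0% | 14.0% | 3.5% | 4.1% |
| 0.7 | 22.8% | 11.9% | 2.7% | 3.6% |
| 0.9 | 16.9% | 8.7% | 2.0% | 2.6% |

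Two assumed spirometry-like correlation matrices gave 24.3% and 25.3% under A, and 12.8% and 13.3% under B. For one active arm against control, rule A gives 17.6% at correlation 0.3 and 9.4% at 0.9.

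**4. Nine cells instead of three arms.** A separate simulation with nine cells of six gave, under the logic of rule B, 0.146 at correlation 0.5 for the three therapy pairs (0.10 to 0.15 for correlations 0.8 to 0.3). For all 36 cell pairs it gave 0.117 (0.09 to 0.12).

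**5. What the gate does once one variable truly changes.** With a shift of 1.2 SD in one arm on one variable, the joint MANOVA rejects in 95.1% of trials at correlation 0.5 and 99.8% at 0.7. Rule C then gives a false positive on one of the other three variables in 11.2% and 9.9% of trials. With a shift of 1.5 SD and correlations 0.3 to 0.9, the figure is about 8-12%. In the nine-cell layout, with only PEFR shifted by 1.5 SD, it is 7.5-10%.

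**The case against.** The strongest reply is that Data analysis puts a MANOVA first and calls the Bonferroni test post hoc. If the MANOVA is joint over the variables and must be significant before anything else is read, the error is about 2-4% when nothing differs. This stands as far as it goes. But the article does not state such a gate. Nor does it say that the MANOVA is joint across variables: the one in Sample size calculation is a repeated-measures test of a single response. The gate also does not protect the remaining variables once one truly changes, and the independent t-tests are not tied to it.

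A reader might infer that the Bonferroni step compares groups within each variable only, and that the trial therefore runs at a flat 10-15% error. The article does not support that. The family is not defined, and correction over all 12 comparisons would keep the rate below 5%. The percentages are conditional on a reading.

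A reader might also count all seven outcomes. The walk test and the two questionnaires are not called primary, so testing them does not inflate the primary claim.

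The simulations use one value per variable, not the planned six-occasion interaction, and assume equal correlations, although the ratio is a function of two of the other variables. That limits precision but does not remove the inflation. The wording on suitability is hedged, as the objection would note, but it is still the conclusion the trial is built to reach.

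Finally, details of an adjustment family may properly sit in an unseen analysis plan. The point does not rest on that detail. The article itself fixes a four-variable primary outcome, adds t-tests with no stated adjustment and sets the 0.05 level.

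**Conclusion.** The point holds in conditional form. From the text alone, the primary outcome is four unranked variables with no deciding variable or time and no rule across them, and unadjusted t-tests against control are planned at 0.05.

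Assuming no true effect, arms of 18 pooled over impairment class and correlations of 0.3 to 0.9, the chance of a false win on at least one variable is:

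- about 16-30% through the unadjusted t-tests, which is the clearest route because it needs no guess about the Bonferroni family;
- about 8-16% if Bonferroni works only within each variable and nothing gates it;
- below 5% under a joint MANOVA gate when nothing differs, but about 8-12% on the other three variables once one truly changes (assumed shift 1.5 SD).

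The open choice of time point is not included in these figures.

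**What to change.** In Sample size calculation and Data analysis, do one of the following:

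- name one deciding spirometry variable and time point, for example FEV1 at the end of week 12, and make the other three secondary; or
- keep all four primary and apply Holm across the four variables on top of the group-pair correction.

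In either case, drop the unadjusted independent t-tests or label them descriptive. State that any claim that one therapy suits an impairment better requires the deciding result.

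The cost is more than wording. A significant result on another variable can no longer carry the conclusion alone, and Holm costs some power with six participants per cell. If a single-time contrast becomes the deciding test, the stated power must be restated for it, because N = 51 was computed for a group-by-time interaction over six measurements. No extra visits or measurements are needed.

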**FIGURE 1 F0001:**
[figure not shown]
F-test multivariate analysis of variance of within/between group interaction.

We intend to investigate the main effects, within and between interactions, for two factors, namely:

Factor A – Therapy with three levels (Therapy A, Therapy B and No Therapy)Factor B – Types of impairments (Obstructive, Restrictive and Mixed) nested within factor A

This gives 3 × 3 = 9 groups of participants from which repeated measurements are to be obtained.

We are also planning to measure three continuous outcomes at different time points of which the minimum repeated measurements are expected to be six per subject for some of the outcomes and a maximum of 36 per subject. Suppose a minimum of six repeated measures is to be obtained from each subject, in that case, it is estimated that a minimum total sample size of 51 patients is required to detect an effect size v = 0.35 with 95% confidence (5% Type I) – similar studies also expected to produce similar results about 80% of the time (Power of test 80%). In the case that during the time of data collection, the hospital experiences a high number of COPD, IPF, ILD, cystic fibrosis, thoracic cage abnormalities patients or resources permit, we are able to increase the total sample size to at most 68 subjects with a corresponding increase in the power of the test to about 95% still detecting effect sizes between 0.3 and 0.4 (see Figure 1). This translates to the possibility of recruiting between five and eight patients per group. Hence, the sample size estimates suggest that recruiting more than eight patients per group for our study will be a waste of resources.

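### The 80% power belongs to a nine-group omnibus test at f(V) = 0.35 and cannot be read as power for a clinically relevant therapy difference in lung function

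*Protocol article*

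**What the plan says.** All references are to the protocol article, section Sample size calculation, including the text after Figure 1.

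- The primary outcome is lung function: "The pulmonary function test is the primary outcome of interest for our study". No single variable is named there.
- The same sentence goes on to "expected clinically relevant difference for obstructive restrictive and mixed impairment using LLN and GLI reference equation". It gives no value, unit or variable. The next sentence opens with an inference word and moves to the software calculation, for which the text sets "confidence level at 5% = 0.05 and effect size of 0.35".
- The software inputs are "Effect size f(V) = 0.35", "α err prob = 0.05" and "Power (1-β err prob) = 0.8", with nine groups and six measurements, for a repeated-measures MANOVA within-between interaction with Pillai's trace. The output is 51 patients and V = 0.5456570. (The running text also gives the power as 95%. The output shows that 80% was used.)
- The nine groups are three therapies by three impairment classes, with class described as nested within therapy. The stated aim covers main effects and interactions of both factors.
- The conclusion drawn is that "51 patients is required to detect an effect size v = 0.35 with 95% confidence", with power of 80%, and that going beyond eight patients per group would not be worthwhile.

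The Abstract plans 54 patients, six per therapy-by-class cell, so 18 per therapy arm.

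**The concern.** A reader of this section will take the 80% as the chance of seeing a worthwhile benefit of one of the devices on lung function. Two things stand in the way.

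First, a lower limit of normal or a reference equation says which spirometry value is predicted or abnormal. It does not supply a difference between therapies to detect, and nothing in the section turns such a difference into 0.35.

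Second, the powered hypothesis is that nine groups have the same course over six visits. That hypothesis can fail through therapy, through class, or through their interaction, in any of five time dimensions. A therapy effect is one small part of it.

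Two misreadings follow. A non-significant omnibus result could be reported as good evidence against a benefit when the test had little power for one. A significant result could be credited to therapy when the classes merely progressed differently.

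**Working it through.** **1. Reproducing the plan's figure.** Inputs from the section: k = 9 groups, 6 measurements (so p = 5 time contrasts), f(V) = 0.35, α = 0.05, N = 51.

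- s = min(k − 1, p) = min(8, 5) = 5
- df1 = 8 × 5 = 40
- df2 = s(N − k − p + s) = 5 × (51 − 9 − 5 + 5) = 210
- λ = s × N × f² = 5 × 51 × 0.1225 = 31.2375
- V = s × f²/(1 + f²) = 5 × 0.1225/1.1225 = 0.5457
- The noncentral F with critical value 1.4522 gives power 0.8011.

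Every printed figure is reproduced, and 51 is the minimum N. At N = 54 the same formula gives 0.835.

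**2. What this V means for a therapy effect.** Assume only the therapy arms differ, equally in all classes, along one time profile. Then V = e/(1 + e), so e = 0.5457/0.4543 = 1.201. With three equal arms and one arm apart from the other two by D, e = D² × 2/9, so D = √(1.201 × 4.5) = 2.32. The unit is the SD of the standardised within-person time contrast. If the effect spreads over two time profiles, the corresponding figure is 1.50.

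**3. Power at the planned size.** Simulation with N = 54, six per cell, five time contrasts, both therapies better than control by d SD of one contrast in every class, α = 0.05, and 2,000 to 4,000 runs per point. Ranges show separate runs.

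| Test | d | Power |
|---|---|---|
| Nine-group by time, 40 df | 1.0 | 0.20–0.22 |
| | 2.0 | 0.75 |
| | 2.1 | 0.78–0.80 |
| | 2.325 | 0.86 |
| Therapy by time, 10 df | 1.3 | 0.79–0.80 |
| Therapy on one pre-planned contrast, 2 df | 0.95 | 0.82 |
| | 1.0 | 0.85–0.87 |

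The 2.32 of step 2 and the 2.1 here agree. The first is the effect the software assumes for 51 patients. With 54 patients, power at that effect is 0.835 by formula and 0.86 by simulation, so 80% is reached at a somewhat smaller effect.

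**4. Rejection without a therapy effect.** The 40-df test treats the nine groups alike, so a class effect of the same size and shape gives the same power. With classes drifting apart by 2 SD of the contrast and no therapy effect, it rejects 75% of the time.

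**5. The unit.** For a gain rising linearly over six equally spaced, equally correlated visits, SD of first-to-last change = d/√1.4. So 2.1/1.183 = 1.8 SD of change. In between-patient SD this is multiplied by √(2(1 − ρ)). The article gives no ρ. Assuming ρ of 0.90 to 0.95, 2.1 becomes 0.79 to 0.56 between-patient SD.

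**6. Class-specific effects.** Suppose the inspiratory device gains d in the restrictive class, the expiratory device gains d in the obstructive class, and both gain d/2 in the mixed class. The 2-df class-adjusted therapy test then has about 30% power at d = 1.0, against 85–87% for the class-common effect. A pairwise t-test within one class (6 v 6) has 80% power only at 1.80 SD of the quantity analysed; for 18 v 18 the figure is 0.96.

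**The case against.** **The article is condensed.** A basis for 0.35 may stand in the full protocol, and the sentence on the clinically relevant difference is grammatically incomplete. That is fair, so the point is not that a derivation is missing. It is that the printed text presents the number as following from such a difference, while the printed inputs contain none.

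**The trial is not about a class-common effect.** The Abstract's clinical implication and the Background ask which device suits which impairment. This stands. A class-adjusted therapy main effect as the only deciding test would lose that question. If the two devices merely cross over between two classes around control, that test rejects about 5% of the time whatever the effect. Any remedy must keep the therapy-by-class-by-time test.

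**Stronger readings that a reader might infer, and that the documents do not support:**

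- That the trial is underpowered for a relevant difference by a known amount. The article gives no relevant difference, SD or visit correlation, so no shortfall can be stated.
- That a therapy must improve lung function by about two between-patient SDs. The 2.1 is in SD of a within-person contrast, under one time profile and an effect shared by all classes. Step 5 of the working shows how far the between-patient figure can differ.
- That the calculation used V = 0.35, because the text after Figure 1 writes the effect size as v. The printed output shows f(V) = 0.35 and V = 0.5456570, and 51 patients matches that. It is loose notation, worth correcting but no more.

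**Conclusion.** The point holds in this form: the sample size arithmetic is correct, but the meaning attached to it is not supported. The 80% is power for a 40-df nine-group-by-time interaction at V = 0.546, and it cannot be read as power for a clinically relevant therapy benefit.

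For a therapy effect common to all classes along one time profile, with 54 patients analysed, that test has about 20% power at 1 SD of the time contrast and about 80% near 2.1 SD. The same patients give about 80% at 1.3 SD on the therapy-by-time test, or at about 0.95 SD if one contrast is pre-planned. These figures assume normal data, equal cells of six and no dropout. They do not carry over to class-specific effects, for which power is much lower.

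This should be changed before results are interpreted, because it alters what a significant or a non-significant omnibus result can be taken to show.

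**What to change.** Keep 54 patients and make two changes.

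1. **Sample size calculation, including the text after Figure 1.** Write the effect size as f(V) = 0.35 (Pillai V = 0.546). Remove the suggestion that it represents a clinically relevant difference. State that the 80% applies only to the nine-group omnibus interaction.
2. **Data analysis.** Treat class as crossed with therapy, not nested in it. Base therapy conclusions on two tests from the same model, therapy-by-time and therapy-by-class-by-time, and not on the nine-group omnibus test. State the detectable difference of each with its unit. For the class-common effect this is about 1.3 SD of the time contrast on the 10-df test, or about 0.95 SD if one contrast is planned in advance. Say plainly that power for class-specific effects is much lower. A figure in lung-function units can be added once a variable, an SD and a visit correlation are chosen and sourced.

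Cost: a rewritten sample size paragraph and a few lines in the analysis section, with no extra patients and no change to treatment or visits. The stated sensitivity becomes less favourable, and two tests replace one, so the plan should say how the two are read together.

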**FIGURE 1 F0001:**
[figure not shown]
F-test multivariate analysis of variance of within/between group interaction.

We intend to investigate the main effects, within and between interactions, for two factors, namely:

Factor A – Therapy with three levels (Therapy A, Therapy B and No Therapy)Factor B – Types of impairments (Obstructive, Restrictive and Mixed) nested within factor A

This gives 3 × 3 = 9 groups of participants from which repeated measurements are to be obtained.

We are also planning to measure three continuous outcomes at different time points of which the minimum repeated measurements are expected to be six per subject for some of the outcomes and a maximum of 36 per subject. Suppose a minimum of six repeated measures is to be obtained from each subject, in that case, it is estimated that a minimum total sample size of 51 patients is required to detect an effect size v = 0.35 with 95% confidence (5% Type I) – similar studies also expected to produce similar results about 80% of the time (Power of test 80%). In the case that during the time of data collection, the hospital experiences a high number of COPD, IPF, ILD, cystic fibrosis, thoracic cage abnormalities patients or resources permit, we are able to increase the total sample size to at most 68 subjects with a corresponding increase in the power of the test to about 95% still detecting effect sizes between 0.3 and 0.4 (see Figure 1). This translates to the possibility of recruiting between five and eight patients per group. Hence, the sample size estimates suggest that recruiting more than eight patients per group for our study will be a waste of resources.

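### The 80% power belongs to a 40-df omnibus over nine cells of a crossed design mislabelled as nested. It is not power for a therapy contrast, and the eight-per-group ceiling drawn from it is unsupported.

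*Protocol article*

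**What the plan says.** All references are to the protocol article.

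- **Factor structure.** The text beside Figure 1, in the sample size section, gives therapy three levels and adds "Factor B – Types of impairments (Obstructive, Restrictive and Mixed) nested within factor A". It then counts 3 × 3 = 9 groups. The Abstract (Method) and the randomisation section divide each impairment class among three groups by ballot, six per cell and 54 in all.
- **Powered test.** The program output is for a MANOVA, "Repeated measures, within-between interaction", with "Effect size f(V) = 0.35", "α err prob = 0.05", "Power (1-β err prob) = 0.8", nine groups and six measurements. It returns 40 and 210 df, N = 51 and power 0.8010637. The sentence introducing it instead gives power as 95%. That is a separate inconsistency; the output corresponds to 0.8.
- **Ceiling.** N may rise to 68, with power of about 95% for effect sizes from 0.3 to 0.4, and "recruiting more than eight patients per group for our study will be a waste of resources".
- **Purpose.** The Background seeks the most suitable intervention for each impairment. The Abstract (Clinical implication) says the results may show "if inspiratory incentive spirometry or expiratory incentive spirometry is better suited for the treatment of the respiratory impairment".

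**The concern.** The design text and the power calculation do not line up with the question.

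First, if impairment is modelled as nested in therapy, the impairment and therapy-by-impairment effects are merged. The interaction that says whether the better therapy depends on the class then has no term of its own.

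Second, the calculation treats the nine cells as one factor. Its interaction with time therefore includes differences in time course between impairment classes, which are not randomised and are not treatment effects.

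Third, the plan uses power for this omnibus to cap recruitment. A reader could take 80% as the chance of detecting a therapy effect, and could take a non-significant comparison of six against six as evidence of no difference.

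**Working it through.** **1. Crossed or nested.** Nesting would require different impairment classes under each therapy. The same three classes occur under all three therapies, and the ballot is run by class. The layout is crossed, with class as a stratum.

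**2. The plan's own figure.** Inputs from the program output: f(V) = 0.35, α = 0.05, nine groups, six measurements. Pillai trace, O'Brien-Shieh form, with p = 6 − 1 = 5, q = 9 − 1 = 8 and s = min(p, q) = 5:

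- df1 = p·q = 40
- df2 = s(N − 9 − p + s) = 5 × (51 − 9 − 5 + 5) = 210
- λ = f²·N·s = 0.1225 × 51 × 5 = 31.2375
- V = s·f²/(1 + f²) = 0.6125/1.1225 = 0.5457
- critical F = 1.4522, power = 0.801 (N = 50 gives 0.789)

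The output reproduces. The word nested does not affect it, because nine groups give 40 df either way.

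**3. What the 40 df contain.** Therapy × time (3−1)(6−1) = 10; impairment × time (3−1)(6−1) = 10; therapy × impairment × time 2 × 2 × 5 = 20. In a simulation with nine cells of six, six time points, 2000 runs per setting, time courses differing by impairment only and no therapy effect, the omnibus rejected in 43%, 82% and 97% of runs at three assumed effect sizes. Therapy × time (4.4–4.6%) and the three-way test (3.7–5.2%) stayed near 5%.

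**4. The claim at N = 68, same omnibus** (df2 = 5 × 59 = 295):

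| f(V) | λ | Power |
|---|---|---|
| 0.30 | 30.60 | 81% |
| 0.35 | 41.65 | 94% |
| 0.40 | 54.40 | 99% |

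At f(V) = 0.30, 95% power needs N = 94, or 94/9 = 10.4 per cell.

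**5. Separate terms at nominal f(V) = 0.35**, with error from the nine-cell model:

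| Term | q = s | N = 51 | N = 54 | N = 68 | V implied |
|---|---|---|---|---|---|
| Therapy × time | 2 | 60% | 64% | 77% | 0.218 |
| Therapy × impairment × time | 4 | 84% | 87% | 95% | 0.437 |

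For example, therapy × time at N = 54: df1 = 10, df2 = 2 × (54 − 9 − 5 + 2) = 84, λ = 0.1225 × 54 × 2 = 13.23.

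These rows do not describe equal effects, because V depends on s. If therapy × time carried the omnibus V of 0.546, then f² = V/(s − V) = 0.375, λ = 0.375 × 2 × 54 = 40.5 and power at N = 54 would exceed 99%. With half that V it is 77%, and with a third 53%.

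**6. Two therapies within one class**, one end-point value per person, two-sided 0.05, non-central t with noncentrality d√(n/2) and 2n − 2 df. The article gives no SD or numeric target difference, so d is an assumption shown as a range:

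| n per cell | d for 80% power | Power at d = 0.5 | d = 0.8 | d = 1.0 |
|---|---|---|---|---|
| 6 | 1.80 | 12% | 24% | 35% |
| 8 | 1.51 | 15% | 32% | 46% |

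With the error pooled over nine cells, the detectable d is 1.65 and 1.42. For 80% power, n per cell is 17 at d = 1.0, 26 at 0.8 and 64 at 0.5.

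**The case against.** The strongest reply has four parts.

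- **The question may already be powered.** At the same nominal f(V), the three-way term, which bears most directly on which therapy suits which class, has 84% power at N = 51 and 87% at N = 54. This stands. A reader might infer that the trial is underpowered for its question, with 60–64% as the true power. The documents do not support that: the 60–64% holds f(V) fixed while s falls from 5 to 2, and nothing in the article settles how the effect divides among terms. Equally, the 87% is for a global 20-df test on an effect size tied to no clinical difference, so it does not establish power for a particular within-class contrast.
- **The label may be harmless.** The article announces main effects and interactions for two factors, the data analysis section specifies no nested model, and model terms are commonly left to an analysis plan. It is also tempting to say that a positive omnibus will be reported as a therapy effect, but the article does not say so. These are risks created by the wording, not stated intentions. The wording is still wrong.
- **The within-class figures are pessimistic.** They use one value per person, whereas 6 to 36 measurements per subject are planned. Baseline adjustment or averaging could lower the detectable difference by an amount that depends on unknown correlations. This stands as a limit on the figures.
- **The ceiling refers to the omnibus.** At f(V) = 0.35, 94% at N = 68 is close to the claim. It fails at the lower end of the article's own range.

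**Conclusion.** The point holds in this form. Nested is wrong: the design is crossed. The arithmetic behind N = 51 is right, but its 80% belongs to an omnibus in which 10 of 40 df are a non-randomised impairment × time effect, so it cannot be quoted as power for a therapy effect or for IIS v EIS within a class. The claim for N = 68 is wrong at the lower end (81% at 0.30). The ceiling of eight per group is unsupported, since a simple within-class comparison at that size reaches 80% power only near 1.5 SD, and near 1.8 SD at the planned six.

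The omnibus results need no assumption beyond the article's inputs. The per-term powers rest on an equal nominal f(V). The within-class figures rest on a single end-point value and an assumed standardised difference. It does not follow that therapy × time must be the sole confirmatory test: which term is confirmatory is a design choice for the sponsor.

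**What to change.** 1. Replace nested with crossed, and describe impairment class as a stratum.
2. Name therapy × time and therapy × impairment × time as separate tests, and state that the 40-df omnibus will not be read as a therapy effect.
3. State that the 80% applies to the omnibus only. Give power for each named term with its effect-size assumption: at nominal f(V) = 0.35 and N = 54, about 64% for therapy × time and 87% for the three-way term, with a note that an equal f(V) is not an equal effect across terms.
4. Report within-class IIS v EIS contrasts with confidence intervals, as low-precision estimates.
5. Correct the N = 68 statement to 81%, 94% and 99% at 0.30, 0.35 and 0.40, and delete the sentence calling more than eight per group wasteful.

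This changes protocol wording and model specification only; patients, visits and data are unaffected. The downside is a less favourable stated power.
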